# Brain Stimulation and Group Therapy to Improve Gesture and Social Skills in Schizophrenia—The Study Protocol of a Randomized, Sham-Controlled, Three-Arm, Double-Blind Trial

**DOI:** 10.3389/fpsyt.2022.909703

**Published:** 2022-07-07

**Keywords:** communication, social cognition, psychosis, theta burst stimulation, transcranial magnetic stimulation, intervention, cognitive remediation, schizophrenia

## Abstract

**Clinical Trial Registration:**

[www.ClinicalTrials.gov], identifier [NCT04106427].

## Introduction

Schizophrenia is characterized by negative (e.g., affective flattening, avolition, low social drive) and positive symptoms (e.g., hallucinations, agitation, delusions) (1–3), as well as, disorganized thinking (4), motor abnormalities (5–7), and impaired cognitive function (8, 9). Social cognition, which refers to psychological processes that allow for the decoding of the behaviors and intentions of others (10–12), is also impaired in schizophrenia (13). In fact, impaired nonverbal communication is a core characteristic of social cognition deficits in patients with schizophrenia. Impaired nonverbal communication in schizophrenia includes limited nonverbal social perception (14–16) and poor gesture performance (17–19). Most importantly, gesture deficits are directly associated with patients’ poor functional outcome (20). This association between gesturing and functioning is the main reason why we believe that establishing treatments, which alleviate gesture deficits are essential to improve patients’ overall functioning and quality of life (21). Such treatments can potentially facilitate societal participation. With the current trial, we want to determine whether combined brain stimulation and group therapy improve schizophrenia patients’ gesture skills and social functioning.

### Gesture Deficits in Schizophrenia

Gestures are an integral feature of communication: they support language production and transmit information on their own (22). Gesture deficits are prevalent in approximately two-thirds of patients with schizophrenia (17, 18, 23). Accumulating evidence suggests that various domains of gesturing are impaired in schizophrenia, including use of gestures (17, 18, 24, 25) and gesture perception (26). In fact, individuals with schizophrenia often use incoherent and fewer gestures (17, 27, 28) and tend to interpret gestures negatively (29, 30).

Gesture deficits in patients are associated with core schizophrenia symptoms, e.g., negative symptoms (24, 27), frontal lobe dysfunction (17, 18), formal thought disorder (23, 31) and working memory impairments (15, 24). At a neural level, gesture processing involves the praxis network, which combines motor- and speech-related brain areas (32, 33). Neuroimaging demonstrated structural and functional alterations in the praxis network in schizophrenia patients with gesture deficits (34–38). Specifically, two areas of the praxis network are linked to gesture deficits in schizophrenia: the inferior parietal lobule (IPL) and the inferior frontal gyrus (IFG) (39, 40). The IPL has been related to motor functioning, as well as cognitive and visuospatial processing (41–43). The IFG has been associated with motor functioning and language production (44).

### Interventions Improving Gesture and Social Skills

#### Brain Stimulation

Repetitive transcranial magnetic stimulation (rTMS) has the potential to (re-)train distinct neural pathways and therefore rehabilitate specific functions in multiple neuropsychiatric disorders (45). Recent studies demonstrated rTMS efficacy across different domains in patients with schizophrenia. For example, rTMS over the supplementary motor area (SMA) ameliorated motor abnormalities (46, 47) and rTMS over the inferior parietal lobe (IPL) improved gesture performance (48). Different rTMS protocols can have different effects on brain function, depending on their frequency and type of stimulation (49).

Theta burst stimulation (TBS) is an innovative rTMS protocol, which requires less time than standard rTMS. There are two types of TBS: intermittent theta burst stimulation (iTBS), which mainly has facilitatory effects and continuous theta burst stimulation (cTBS), which has inhibitory effects. A pilot study demonstrated that inhibitory cTBS over the right inferior parietal lobe (rIPL) improved gesture performance by comparing 3 rTMS protocols (including sham stimulation) in 20 patients (48). Due to interhemispheric rivalry, cTBS on the right IPL may induce a facilitatory effect on left IPL through transcallosal disinhibition (50). As such, inhibitory cTBS over the rIPL is a promising method to reduce gesture deficits in schizophrenia. We decided to use the same cTBS protocol for repetitive administration in a larger sample.

#### Social Cognitive Remediation Therapy

Social cognition is a main driver of recovery and functional outcomes (10, 51–53) and mediates the relationship between neurocognition and social functioning in schizophrenia (53). The MATRICS initiative (Measurement and Treatment Research to Improve Cognition in Schizophrenia) of the National Institute of Mental Health (NIMH) identified the most important cognitive domains in schizophrenia (10, 54). These consist of *six neurocognitive domains*: speed of processing (1), attention/vigilance (2), working memory (3), verbal learning (4), visual learning (5) and reasoning/problem solving (6) and *five social-cognitive domains*: emotion processing (1), social perception (2), theory of mind (3), social schemata/knowledge (4) and social attribution styles (5). Therapies focusing on both neurocognition and social cognition are suggested to be a promising approach to help patients with schizophrenia (55–57).

One of the few integrative cognitive remeditation therapies (CRT) covering *all* MATRICS domains is the Integrated Neurocognitive Therapy (INT) (58, 59). This CRT approach takes place in a group setting, including social interactive tasks and computerized neurocognitive exercises (using the Cogpack program). INT showed good feasibility with reduction of positive symptoms, negative symptoms and relapses, as well as, improvements in social cognition, neurocognition, and overall functioning in patients with schizophrenia (56, 60–62). The INT includes four modules, each addressing various cognitive domains: processing speed, attention, and perception of emotions (1); verbal and visual learning, memory, social perception, and theory of mind (2); reasoning, problem solving, and social schema (3); working memory and the ability to attribute appropriate meanings (4). INT focuses on the improvement of both social cognition and neurocognition, with more focus on the latter.

Social cognitive remediation therapy (SCRT) is an approach focusing mainly on social cognition in patients with schizophrenia (58, 63). As of today, two types of SCRTs are being developed: *targeted* and *broad-based* SCRTs. Targeted SCRTs address only the remediation of one specific social cognitive deficit (e.g., facial affect recognition) (64), whereas broad-based SCRTs address multiple social cognitive domains (65). Integrative broad-based SCRTs combine the improvement of social cognitive domains with other therapy techniques, such as Cognitive Behavioral Therapy (CBT) (66), cognitive remediation (67, 68) or social skills training (69–71). It is advisable to use an integrative approach involving both neurocognitive *and* social-cognitive domains, as these lead to greater generalization effects on functional outcome (53, 72, 73). In light of previous studies, we consider integrative broad-based SCRTs a promising treatment to reduce social cognitive impairments and enhance functioning in schizophrenia. Therefore, we decided to use this type of treatment approach for the current study.

## Methods

### Aims and Hypotheses

This study’s main goal is to determine the effects of combined cTBS over rIPL and SCRT on gesture performance and social functioning in patients with schizophrenia. In addition, we aim to investigate neurocognitive, social cognitive, motor, clinical and neural effects of both interventions as secondary outcome measures. As cTBS enhances neuroplasticity and improves use of neural resources (46, 74), we expect administration of cTBS to facilitate SCRT training effects. Additionally, we hypothesize that the expected improvement of gesture performance will have positive effects on functional outcome, as both have been reported to be linked in schizophrenia (20). At the neural level, we hypothesize that the brain activity of patients will converge to the brain activity of healthy controls after both interventions, especially within the praxis network (39, 40).

This randomized controlled trial (RCT) will include three patient groups (see Figure 1). First, group A will receive real cTBS and real SCRT. Second, group B will receive sham cTBS and real SCRT. Third, group C will receive no cTBS and sham SCRT. In this study, we will also include a fourth group consisting of healthy controls, who will be assessed twice without any intervention in between. We expect the combination of cTBS and SCRT to show positive effects on both primary and secondary outcomes in patients with schizophrenia spectrum disorders. As such, we expect group A to have superior performance over group B and C in gesture performance and functional outcome after intervention (A > B > C).

**FIGURE 1 F1:**
[figure not shown]
Study Setup. We will randomize 72 schizophrenia patients in three different groups (24 patients per group). Group A will receive real cTBS and real SCRT. Group B will receive sham cTBS and real SCRT. Group C will receive no cTBS and sham SCRT. Both sham treatments are inactive interventions that mimic as closely as possible the real treatments. Group A and B will receive 10 cTBS sessions during the first two weeks of intervention. Additionally, Group A–C will receive 16 SCRT sessions for eight weeks. Outcomes will be measured during four different time points: baseline, after cTBS (week 2), after SCRT (week 8) and follow-up (week 32). We will also include a fourth group consisting of 24 healthy controls, who will be assessed twice (baseline and week 8) without any intervention in between.

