### Statistical Considerations and Plan

Assuming a medium effect size (*f* = 0.15) in a repeated measures ANOVA with moderate-high correlation between time points (0.75), a power of 0.95 and an alpha = 0.05, we will need 72 patients (24 per group). In addition, a control group of 24 healthy subjects will be required. All four groups will be compared pre-to-post with an interval of 8 weeks (see Figure 1). The main effects of the combined interventions on the primary and secondary outcomes will be calculated in a repeated measures design including 3 main time points (Baseline, week 2, and week 8) and three patient groups (A, B, and C). With the latest SPSS and R versions, we also will run additional (partial) correlations, linear regressions, MANCOVAS using covariates (e.g., age, education, and medication).

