### Trial Status

Study recruitment started on the 17th December 2019. The first group started with both interventions on the 24th February 2020. The study was impacted by the federal measures against the COVID-19 pandemic. As of June 2022, we recruited 65 patients and 36 healthy controls. We completed baseline assessments with 62 patients and 33 healthy controls. We finished week-8 assessments with 36 patients and 32 controls.

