### Limitations

This RCT entails a few limitations. First, we cannot eradicate the influence of medication; most patients suffering from schizophrenia are on antipsychotic treatment and other medication (e.g., blood pressure suppressants, antidepressants). However, for antipsychotic medication, we will control for Olanzapine equivalents in our statistical analyses. Second, we cannot eliminate gains linked to repeated test exposure as a result of retaking the same test under comparable conditions (i.e., retest effects). We counter these effects by randomizing the order of our test items for most of our assessments. Additionally, the time between most of our assessments makes training effects quite unlikely (i.e., 8 weeks, 32 weeks). Third, some of the data we collect are self-reports. Due to the subjective nature of self-reports, their psychometric aspects (e.g., reliability and validity) can be questionable or subject to biases (e.g., response bias). However, self-reports are necessary. For example, it is essential to compare patients’ subjective symptoms before and after intervention to find out if we are helping them. Fourth, another concern is the generalizability of the trial results. Participation in our study is only appropriate for a subgroup of schizophrenia patients, as it consists of 30 meetings in 3 months. As such, we can only include stable outpatients with good time management, commitment and tolerance to additional stress. This might cause the data collection to become arduous and dropout rates to be high.

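### The 72 patients to be randomised are exactly the number needed with complete data, so the stated power of 0.95 leaves no room for the dropout that the article says may be high

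*Protocol article*

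**What the plan says.** Four places in the protocol article bear on this.

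- **Statistical Considerations and Plan, assumptions.** The calculation opens with "Assuming a medium effect size (*f* = 0.15) in a repeated measures ANOVA with moderate-high correlation between time points (0.75" and concludes with "a power of 0.95 and an alpha = 0.05, we will need 72 patients (24 per group".
- **Statistical Considerations and Plan, main analysis.** The effects on the primary and secondary outcomes are to be estimated in a repeated measures design "including 3 main time points (Baseline, week 2, and week 8) and three patient groups (A, B, and C".
- **Figure 1 (Study Setup).** The number to be randomised is the same as the number needed: "We will randomize 72 schizophrenia patients in three different groups (24 patients per group".
- **Limitations.** After describing the burden of participation (30 meetings over three months), the authors write: "This might cause the data collection to become arduous and dropout rates to be high". They give no rate.

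The article states no expected dropout rate, no inflation of the sample size and no rule for replacing patients who leave.

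**The concern.** A sample size meant to withstand dropout is normally larger at randomisation than the number the power calculation requires. Here the two are identical. Unless the calculation has slack in it, the trial drops below its stated power with the first incomplete patient.

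The article itself raises the possibility of high dropout, so its power statement and its own expectation do not fit together. This is more than detail left to a fuller document, because the article gives the required number, the randomised number and the dropout warning explicitly. What is at stake is the figure readers will use to interpret a null result: a missed effect would be judged against a 5% chance of a miss when the real chance may be two or three times that.

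**Working it through.** **Inputs**

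| Input | Value | Source |
|---|---|---|
| Effect size f | 0.15 | Statistical Considerations and Plan |
| Correlation ρ between time points | 0.75 | same |
| Alpha, target power | 0.05, 0.95 | same |
| Groups k, time points m | 3, 3 | same, main analysis |
| Number randomised | 72 | Figure 1 |
| Sphericity | ε = 1 | assumption, not stated |
| Dropout rate | 5% to 40% | assumption, not stated |

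**Step 1. Reproduce the plan's figure.** For the group-by-time interaction in a repeated measures ANOVA, power comes from the noncentral F distribution with

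- λ = f² · N · m / (1 − ρ) = 0.0225 · N · 3 / 0.25 = 0.27 · N
- df1 = (k − 1)(m − 1) = 4
- df2 = (N − k)(m − 1) = 2(N − 3)

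At N = 72, λ = 19.44 and df2 = 138, giving power 0.952. At N = 71, λ = 19.17 and df2 = 136, giving power 0.949. So 72 is the smallest N that reaches 0.95, and it is already divisible by three.

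**Step 2. Check that no margin is hidden in another version of the calculation.** With three groups and the same inputs, the minimum N for 0.95 is:

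- interaction with two time points: 89
- interaction with four time points: 61
- within-patient effect with three time points: 59
- between-group effect: more than 550

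Of these, only the three-by-three interaction gives 72, and it matches the design described for the main analysis. The stated figure is therefore the complete-data number.

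**Step 3. Power if 72 are randomised and only complete patients count.** Completers are 72 · (1 − d), rounded.

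| Assumed loss d | Completers | λ = 0.27 · N | Power |
|---|---|---|---|
| 0% | 72 | 19.44 | 0.952 |
| 5% | 68 | 18.36 | 0.939 |
| 10% | 65 | 17.55 | 0.927 |
| 15% | 61 | 16.47 | 0.908 |
| 20% | 58 | 15.66 | 0.891 |
| 25% | 54 | 14.58 | 0.864 |
| 30% | 50 | 13.50 | 0.832 |
| 40% | 43 | 11.61 | 0.760 |

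The chance of missing the assumed effect rises from 1 − 0.952 = 0.048 with complete data to 1 − 0.891 = 0.109 at 20% loss, a ratio of about 2.3. At 30% loss it is 0.168, a ratio of 3.5.

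**Step 4. Where power crosses the usual benchmarks.** The smallest N for 0.90 is 60, that is 12 of 72 lost (17%). The smallest N for 0.80 is 47, that is 25 of 72 lost (35%).

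**Step 5. Sensitivity to sphericity.** ε = 1 is the favourable value. With ε = 0.75 (λ and both degrees of freedom multiplied by 0.75), power at the full 72 would be 0.897. The figures in Step 3 therefore do not exaggerate the problem on this account.

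**The case against.** The strongest case against the point has four parts.

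- **The arithmetic is right.** The 72 reproduces, and no number in the article is miscalculated. That stands: the fault lies in using the complete-data number as the number to randomise while warning of dropout.
- **The starting power is generous.** Power stays above 0.80 until about a third of patients are lost. This also stands, and it is why the point is not critical. It does not make 0.95 the right figure to report.
- **The warning is tentative.** The authors say that dropout might be high, give no rate, and say they can include only stable and committed outpatients. It would be too strong to say that they predict high dropout. A warning is still enough to call for an allowance or a restated power.
- **Complete-case analysis is not stated.** ANOVA is named only for the power assumption. The main analysis is called a repeated measures design, which a mixed model would also fit, and missing-data handling may be set out in a document not shown. So Step 3 shows the loss for complete cases and does not describe a stated rule of list-wise deletion. A mixed model would generally lose less, but 0.95 would still need essentially full data.

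A reader might also go further and infer a retention rate from Trial Status, which reports 62 patients with baseline completed and then "We finished week-8 assessments with 36 patients and 32 controls". That inference is not supported. Recruitment and follow-up were still running in June 2022, treatment starts in blocks once enough patients are available, and the pandemic had affected the study. The 62 − 36 = 26 patients without a week-8 assessment could all have been waiting or in treatment, so these counts fit full retention as well as heavy loss.

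**Conclusion.** The point holds at moderate severity. The number required and the number randomised are both 72, and 72 is the exact minimum for 0.95 with complete data. With dropout acknowledged as possibly high and no allowance stated, the 0.95 is not the power the design can be expected to deliver.

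The size depends on a dropout rate that the article does not give. Over an assumed 10% to 30% loss, complete-case power for the interaction is about 0.93 to 0.83. This rests on sphericity and on counting only patients with TULIA at baseline, week 2 and week 8. If partial data are used, these values are a conservative guide.

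A reader might also infer that dropout will differ between arms and bias the comparison. Nothing in the article reports or predicts this, so it forms no part of the finding.

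**What to change.** 1. **State an assumed dropout rate to week 8 and its basis, and restate power at the expected number of completers in place of 0.95.** For complete cases with 72 randomised, that is about 0.93 at 10% loss (65), 0.89 at 20% (58) and 0.83 at 30% (50). The choice of rate is the sponsor's.
2. **Specify the main analysis as a likelihood-based mixed model for repeated measures that uses all available TULIA data from all randomised patients.** This limits the loss without extra enrolment. The complete-case values above can be kept as a labelled conservative guide.

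The cost is a few sentences in the protocol or analysis plan and a less favourable power figure.

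The alternative is to keep 0.95 and randomise 72/(1 − d). That is 72/0.9 = 80 at 10% loss (81 for equal groups), 72/0.8 = 90 at 20%, and 72/0.7 = 102.9, so 103, at 30% (105 for equal groups). It costs 9 to 33 additional patients and is not needed if the lower power is acceptable and reported.

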### Setting and Enrollment

#### Study Design

This will be a three-arm, double-blind, randomized, sham-controlled trial of add-on brain stimulation and SCRT to improve nonverbal communication skills and overall functioning in schizophrenia spectrum disorders. This single-site trial will be conducted at the University Hospital of Psychiatry and Psychotherapy, Bern.

#### Study Population

Patients will be asked for participation at the outpatient departments of the University Hospital of Psychiatry and Psychotherapy, Bern and will be screened with the Structured Clinical Interview for DSM-5 (SCID). Healthy participants will be recruited by word-of-mouth and flyers in public places (e.g., grocery stores, pharmacies, gyms) in Bern. Participants will be eligible for study entry if they meet the criteria listed in Table 1.

**TABLE 1 T1:** Eligibility.

Inclusion criteria
Age between 18 and 65 years
Right-handedness
*Patients only:* diagnosis of schizophrenia spectrum disorders according to DSM-5
**Exclusion criteria**
Substance abuse or dependence other than nicotine
Past or current medical or neurological conditions associated with impaired or aberrant movement, such as brain tumors, stroke, Parkinson’s disease, Huntington disease, dystonia, or severe head trauma with subsequent loss of consciousness.
Epilepsy or other convulsions
History of any hearing problems or ringing in the ears
Standard exclusion criteria for MRI scanning and TMS, e.g., metal implants, claustrophobia
Women who are pregnant or breast feeding or intention to become pregnant during the study
Previous enrollment into the current study
*Patients only:* any TMS treatment in the past 3 months
*Patients only:* any cognitive remediation therapy in the past 2 years
*Controls only:* history of any psychiatric disorder or any first-degree relatives with schizophrenia spectrum disorders.

### Interventions

#### Implementation of Real/Sham Continuous Theta Burst Stimulation

Patients will receive ten cTBS sessions in total during the first 2 weeks of intervention. Each session (sham and real cTBS) will last 17 min consisting of two 44 s stimulations over rIPL separated by a 15-min break. For each stimulation of 44 s, we will apply 801 pulses at 50 Hz over the right IPL at an intensity of 100% of the resting motor threshold. Hence, the entire session will consist of 1,602 pulses. Sham cTBS will be delivered with a placebo-coil without any magnetic emission.

#### Implementation of Real/Sham Social Cognitive Remediation Therapy

Real/sham SCRT will be conducted bi-weekly for 8 weeks, totaling 16 sessions of 90 min. Each group will consist of six to eight patients led by a head-therapist (VC) and a co-therapist (FW). INT-expert (DM) will train both therapists and supervises the course of the sessions.

For this trial, we will tailor an SCRT based on the INT manual (58, 59). This SCRT will include the entire social cognitive part of the original INT (consisting of a minimum of 30 sessions) and two INT neurocognitive modules. As such, we will use psychoeducation and Cognitive Behavioral Therapy for Psychosis (CBTp) techniques. This intervention will have the main goal of improving gesture deficits in schizophrenia and will be separated in five blocks; each including neuro- and social cognitive MATRICS-domains (see Table 2). The first, third and fifth block will focus predominantly on using and interpreting nonverbal cues in social contexts. The second and fourth blocks will address memory and attention, both of which are essential for functioning in social interaction. Three sessions will be dedicated to each block, totaling 15 sessions overall. With each session, the content of the blocks will increase in complexity. A final 16th session will be added, in which the content delivered in all previous five blocks will be summarized.

**TABLE 2 T2:** SCRT therapy contents a trained cognitive processes.

	Introductory session: Psychoeducation topics	Training session: Compensation and restitution sessions with interactive and computerized exercises	Transfer session: Practicing coping strategies in daily life with homework
*Block 1:* *Emotion perception and expression*	Six basic emotions: their function, their expression (e.g., gestures) and their effect on perception/attention	Affect recognition and affect expression	Practicing newly learned affect recognition strategies with their regular environment
*Block 2:* ** *Verbal/visual learning and memory* **	Short term memory, long term memory and prospective memory	Mnemonic strategies (e.g., chunking, external memory aids such as calendars and post-its)	Practicing familiar and newly learned mnemonic strategies
Block 3: Social perception and theory of mind	Key social stimuli and theory of mind	Observation of social encounters (e.g., with pictures, videos, and role play) and interpretation of social information	Practicing a more fact-oriented social perception (rather than assumptions-based) with their regular environment
Block 4: Working memory	Selective attention, working memory and how to reduce distractibility	Cognitive flexibility, selective attention, ability to inhibit cognitive interference (e.g., with computer tasks)	Practicing newly learned attention-focusing strategies
Block 5: Social schema	Norms and roles on social behavior and use of social knowledge	Social norms and behavioral sequences (e.g., with role play), recognition of own norm-deviating behavior and building strategies to change it if necessary, as well as coping with social stigma	Practicing newly learned social strategies in role play during group therapy and with their regular environment

Each block will start with an introductory session, followed by a training session (i.e., compensation and restitution sessions), and a transfer session (see Table 2). During the introductory sessions, the MATRICS domains will be presented with a great focus on their everyday use and individual self-reference. The introductory sessions include psychoeducation on the respective neurocognitive and social domains. During the training sessions, we will determine patients’ strongest coping strategies, establish solution-oriented awareness, and train cognitive domains with various exercises (e.g., computerized cognitive tasks or role play exercises). The transfer sessions will work on the principle “rehearsal learning” (75, 76), meaning patients repeatedly apply the newly learned strategies in their daily life to restore social cognitive functions. The treatment goal will be to develop more coping strategies and enhance social skills to increase overall functioning. The therapists will follow a script for quality assurance and treatment fidelity.

Sham SCRT will consist of psychoeducation on sleep hygiene, exercise, stress, and music, as well as leisure activities, and mindfulness-based exercises (e.g., raisin meditation or walking meditation in a nearby park in Bern). Patients receiving this group therapy will also benefit from an interactive environment. The main difference with the real SCRT will be that sham SCRT will not include any (social) cognitive training, nor active transfer of skills into daily life.

